#### Care provisions for patients experiencing harm

In the unlikely event a participating subject experiences an injury from participating in this study, the cost for any required treatment will be billed to that patient or their medical or hospital insurance. The Ohio State University has no funds set aside for the payment of health care expenses for this study.

### Randomization and blinding

Eligible participants who have provided informed consent will be randomized 1:1:1:1 to 0.5, 2.5, or 5 mg/kg/dose citicoline or placebo. Randomization will be completed in permuted blocks of variable size. Each subject will receive a computer-generated randomization ID number, which will be provided to the research pharmacy, where the appropriate test agent will be prepared. Test agent will be labeled with the ID number and date only.

Patients, treating clinicians, trial personnel, and outcome assessors will be blinded to group assignment until after the database is locked and blinded analysis is completed.

### Data management

#### Data collection plan

Data will be collected and managed using REDCap (Research Electronic Data Capture), which is a secure, web‐based electronic system for data entry, integration, processing, and reporting^(144, 145)^. In addition to generating and tracking on‐line case report forms, REDCap allows data validation (through checks on variable formatting and range and logic checks), query generation and tracking, and reporting. REDCap is easy to navigate and has been historically vetted for security and HIPAA compliance. REDCap also has functionality to store source documents, enabling staff and PI access to key study documents and improving operational workflows. Data access will be defined and tightly controlled according to each person’s role (blinded, unblinded). Advanced data filtering functions will ensure that staff have access to appropriate data while reducing the likelihood of unblinding. Data and data labels can be downloaded selectively (for interim progress reports) or in their entirety (at end of study) directly from REDCap in SAS or Excel format.

Data will be collected prospectively by study staff using the EMR. Following verification, data will be locked. Data access will be defined and tightly controlled according to each person’s role (blinded, unblinded).

#### Quality assurance and quality control

The clinical research manager will perform internal quality management of study conduct, data and biological specimen collection, documentation, and completion. Quality control procedures will be implemented beginning with the data entry system and data quality control checks that will be run on the database will be generated. Any missing data or data anomalies will be communicated to the PI for clarification/resolution.

Following written Standard Operating Procedures, study monitors will verify that the clinical trial is conducted, data are generated, and biological specimens are collected, documented (recorded), and reported in compliance with the protocol, International Conference on Harmonisation Good Clinical Practice, and applicable regulatory requirements (e.g., Good Laboratory Practices and Good Manufacturing Practices).

#### Access to source data

Documentation of source data is necessary for the reconstruction, evaluation and validation of clinical findings, observations, and other activities during a clinical trial. The original documentation where subject information, visits consultations, examinations, and other information are recorded are all considered source documents and source data. The PI and site staff will make all source documents, data, and reports available for inspection to the NIAID, as well as to relevant local and regulatory authorities for the purpose of monitoring and auditing. All representatives of these entities are bound to maintain the strict confidentiality of medical and research information that may be linked to identified individuals.

### Statistical analysis

All analysis will be based on intention to treat guidelines and reporting will follow CONSORT guidelines [65]. Data will be analyzed using STAT software (SAS; Cary, NC). The primary clinical outcome (S:F ratio on day 3) will be analyzed using either analysis of variance or a non-parametric Kruskal–Wallis test if analysis of variance assumptions (normality, homoscedasticity) are violated. Follow-up contrasts comparing each dose to control will be performed at *α* = 0.05/3 if the global test of differences between groups is rejected. If subject dropout due to mortality or discharge is present prior to day 3, the survivor average causal effect will employ a potential outcomes approach to account for potential survival bias and estimate the average causal effect of the intervention on S:F ratio among participants who would survive regardless of their intervention status, e.g., the always-survivors [66, 67]. The recommended citicoline dose for Phase 3 trials will be the dose achieving the greatest statistically significant improvement in day 3 S:F ratios, with consideration of key secondary endpoints (SOFA scores, etc.). Standardized mean differences will assess balance on baseline covariates across treatment arms. Competing risks analysis will assess differences between groups for competing time-to-event outcomes (e.g., hospital mortality, time to recovery, time off ventilator, discharge) [68].

Differences in SOFA scores between groups will be evaluated using non-parametric tests. A multinomial ordinal proportional odds model will estimate the odds ratio between study groups for COVID Ordinal Outcomes Scale. For outcomes with repeated assessments, generalized mixed models will evaluate differences between groups with a subject-level random effect to account for repeated measures. The mixed model accounts for data that are missing at random, when including baseline covariates associated with missing status. To account for potential non-ignorable dropout (e.g., due to mortality), a joint modeling approach will incorporate a shared random effect to simultaneously model the time-to-event process and longitudinal process [69].

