#### Participant timeline

The timing of study procedures is based on the time at which consent was obtained, which is defined as “Time 0”. Chest X-ray will be performed and baseline Sequential Organ Failure Assessment (SOFA) and COVID Ordinal Outcomes Scale (HRS) scores will be calculated at Time 0. Study test agents will be administered by study personnel while the patient is hospitalized, with the first dose being administered within 4 h of Time 0. If the patient is discharged prior to completion of the study medication, no further study medication will be administered.

Individual patient schedules are shown below and in Fig. 2.

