#### Protocol modifications

Any modifications to the approved clinical protocol will be developed in consultation with the DSMB and will be implemented only after approved by the OSU IRB and FDA. Once the protocol change is approved by the IRB, the DSMB and NIAID will be notified.

The PI will then schedule an educational session to review changes in the protocol with the participation of each team member recorded.Sample size. Sample size calculations are based on differences in % carotid S_p_O_2_ between saline and CDP‐choline treatment groups in SARS CoV‐2-infected mice (unpublished data). Effect sizes post treatment were 1.32 in IAV and 1.4 in SARS CoV‐2 infected mice. With 24 subjects in the 2.5 and 5 mg/kg/dose treatment groups and 24 controls, and allowing 5% missing data at day 3 (80 participants total), there is 80% power (*α* = 0.05) to detect an effect size of 0.9 in S:F ratio between any individual arm and control (0.39 effect size overall), 32% below that in our preliminary data.

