There are some limitations to the SCARLET study. COVID-19 has a broad spectrum of clinical severity, so designing a pilot trial with statistical power to detect a meaningful difference in ICU-free days or mortality as primary outcome would require an unfeasibly large sample size and could miss significant beneficial effects of citicoline in hospitalized patients. Likewise, the COVID Ordinal Outcomes Scale score [100] would be underpowered to assess efficacy in a small study. As most COVID-19 morbidity relates to HARF and the greatest experimental effect of citicoline is on S_p_O_2_ in mice infected with both IAV [58] and SARS CoV-2 (unpublished observations), we chose to use the lowest S:F ratio value on study day 3 as our primary efficacy readout. P:F and S:F ratios are closely correlated and essentially interchangeable [101–103]. P:F ratios can also be imputed from S_p_O_2_ values [102, 104, 105]. Changes in both are highly and comparably predictive of ICU mortality in ARDS [104]. Lower S:F ratios are also highly predictive of ICU mortality in COVID-19 patients [106, 107].

As a secondary efficacy readout, we will also evaluate the impact of citicoline treatment on SOFA scores in enrolled patients. The SOFA score comprises 0 to 4 points assigned to each of 6 organ systems, based on P:F or S:F ratio, Glasgow Coma Scale score, mean arterial pressure, serum creatinine, serum bilirubin, and platelet count [108]. Higher SOFA scores indicate worse organ function. Although originally designed for sepsis patients, and not universally accepted as being of prognostic value in COVID-19 [109], multiple studies have shown associations between elevated SOFA scores and poor outcomes in this population [110–115]. Moreover, the multisystem nature of the SOFA score may allow us to identify beneficial effects of citicoline on other organs.

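### The primary test of day-3 S:F omits the baseline value and puts a global gate in front of Bonferroni contrasts, giving away power that ANCOVA with Dunnett contrasts would recover without extra patients

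*Protocol article*

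**What the plan says.** The Statistical analysis section fixes the primary test: "The primary clinical outcome (S:F ratio on day 3) will be analyzed using either analysis of variance", or a Kruskal–Wallis test if normality or equal variance fails. No covariate is named. Dose-versus-control contrasts follow, and these "will be performed at *α* = 0.05/3 if the global test of differences between groups is rejected". Baseline covariates do appear in the same section, but only for balance checks by standardized mean differences and in the mixed models for repeated outcomes.

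Other sections bear on the point:

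- **Study design and setting:** 20 patients in each of four arms.
- **Randomization and blinding:** permuted blocks of variable size, with no strata named.
- **On-study monitoring:** SpO2 is recorded every 2 minutes.
- **Participant timeline:** baseline SOFA and ordinal-scale "scores will be calculated at Time 0". The Discussion explains that the respiratory item of SOFA uses P:F or S:F.
- **Discussion:** in explaining the choice of endpoint, the authors note that "COVID-19 has a broad spectrum of clinical severity".
- **Protocol modifications (sample-size text):** 80% power at alpha 0.05 for an effect of 0.9 between any one arm and control (0.39 overall), with 80 participants and 5% missing at day 3.

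**The concern.** Two features of the primary analysis cost power in a small trial.

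First, patients will enter with differing oxygenation, and some of the day-3 variance will reflect where they started. An unadjusted comparison leaves that variance in the error term. Without stratification, and with 20 per arm, chance differences in baseline S:F also pass unadjusted into the dose estimates. A balance table can show such a difference but does not correct the comparison.

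Second, each dose contrast must pass two controls: the global test and then a Bonferroni-split alpha. The split alone already holds the familywise error at 5%. So would Dunnett's procedure, which uses the correlation created by the shared control arm.

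The dose for Phase 3 is to be the one with the greatest statistically significant gain in day-3 S:F, with secondary endpoints considered. A low-powered, unadjusted contrast therefore weakens both the efficacy signal and the dose choice.

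**Working it through.** **Inputs.** From the protocol: four arms, 20 per arm, 5% missing (80 × 0.95 = 76, so 19 per arm), effect d = 0.9, overall f = 0.39, alpha 0.05, contrasts at 0.05/3 after a global rejection. Assumed: two-sided tests, a global test at 0.05, normal outcomes, and baseline-to-day-3 correlation r from 0 to 0.7. The sample-size text also mentions 24 per group, which does not fit 20 per arm and 80 in total; the design figure of 20 is used here.

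**1. The plan's own figure.** One arm shifted by 0.9 and three equal gives f = 0.9 × √3/4 = 0.390. The global F test with 3 and 72 df and noncentrality 76 × 0.39² = 11.6 has power 80.2%. The stated 80% therefore reproduces for the global test. It also reproduces for a single contrast at unadjusted 0.05 with 20 per arm (80.2%, pooled t).

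**2. Power of the contrasts as planned.** The noncentrality is 0.9/√(2/19) = 2.774. The Bonferroni critical value at 72 df is 2.451, which gives about 63%. Requiring the global rejection as well gives 61% by simulation.

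**3. Dunnett without the gate, unadjusted.** The critical value by simulation is about 2.40, which gives 65%.

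**4. Baseline adjustment added.** Under ANCOVA the residual SD shrinks by √(1 − r²), so the noncentrality becomes 2.774/√(1 − r²), with one fewer df.

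| r (assumed) | Noncentrality | Power, ANCOVA + Dunnett | Equivalent n per arm, 20/(1 − r²) |
|---|---|---|---|
| 0 | 2.77 | 64–65% | 20 |
| 0.3 | 2.91 | 68–69% | 22 |
| 0.4 | 3.03 | 73% | 24 |
| 0.5 | 3.20 | 78–79% | 27 |
| 0.6 | 3.47 | 85% | 31 |
| 0.7 | 3.88 | 93% | 39 |

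Ranges show simulation and noncentral-t results where they differ. Power of 80% needs r of about 0.52 with 19 per arm, or 0.48 with 20. Without adjustment, the contrasts at 0.05/3 would need 27 evaluable patients per arm.

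**5. Other response patterns, unadjusted, 19 per arm (simulation).**

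| Pattern | Quantity | Gate + Bonferroni | Bonferroni, no gate | Dunnett, no gate |
|---|---|---|---|---|
| Graded 0.3, 0.6, 0.9 | Any-dose power | 61% | 67% | 69% |
| All doses 0.9 | Any-dose power | 80% | 85% | 86% |
| No effect | Familywise error | 3% | 4% | 5% |

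The gate costs most when several doses work, and it holds the error well below the 5% allowed.

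**6. Chance imbalance.** The SE of a baseline difference between two arms of 20 is √(2/20) = 0.316 SD. P(|difference| > 0.3 SD) = 2 × [1 − Φ(0.3/0.316)] = 34% for any one dose-control pair.

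**The case against.** The strongest reply is that nothing here is invalid. ANOVA followed by Bonferroni contrasts is conventional and conservative, and this trial seeks preliminary evidence. That stands: the point is about efficiency, not error control.

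Second, the gate and the Bonferroni split matter less than the missing covariate. For a single effective dose, removing both moves power only from 61% to 65%. That also stands. Most of the gain comes from adjustment and depends on a correlation the protocol does not give. The correlation could be low, because the outcome is taken at the lowest SpO2 of day 3 while the covariate would come from a short pre-dose window. At r = 0.3 the full change reaches only 68–69%, so recovering power does not mean reaching 80%. Even at r = 0, however, the revised analysis does not fall below the planned one.

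Third, chance imbalance is already part of the unadjusted variance, so it is not a loss on top of the 61%. At r = 0.5, a 0.3 SD imbalance shifts the contrast by 0.5 × 0.3 = 0.15 SD, one-sixth of the target. This is fair. Imbalance explains how an individual result can mislead; it does not bias the test over repeated trials.

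Fourth, the remark on the spectrum of severity was made to justify the endpoint, and the eligibility criteria narrow the sample. Even so, the secondary outcomes cover extubation and ventilator-free, ICU-free and oxygen-free days, which implies a wide range of respiratory support among those enrolled.

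Finally, no baseline S:F variable is named, and day-1 values may be post-dose. One must be defined, but its components come from routine monitoring and the record.

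**Conclusion.** The concern holds as an efficiency weakness that should be corrected. The planned procedure has about 61% power for a dose with a 0.9 SD effect at 19 per arm. Dunnett without the gate gives about 65%, and adding the baseline covariate gives about 73% to 85% for r between 0.4 and 0.6. The direction is secure: power rose in every scenario examined, including r = 0. The size rests on the assumed correlation, on normal outcomes and on 5% missing data. Type I error control is not in question. Death or discharge before day 3 is a separate problem that this change does not solve.

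**What to change.** Amend the Statistical analysis section as follows:

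1. Define a baseline S:F from one stated pre-dose window at Time 0, by a fixed rule for choosing the SpO2 reading and its concurrent FiO2.
2. Make the primary analysis an ANCOVA of day-3 S:F on arm and baseline S:F, with the three dose-control contrasts by Dunnett at two-sided familywise 0.05.
3. Drop the global test as a gate and report it descriptively.
4. If a non-normal fallback is kept, make it the same model on ranks, with the trigger written down and judged on pooled blinded data.
5. State how the adjusted model fits with the survivor average causal effect analysis.

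The cost is analysis wording, one variable definition (including retrieval for patients already enrolled) and one degree of freedom. If r were zero, adjustment would lose at most about one point against unadjusted Dunnett. The article reports 15 of 80 enrolled and blinding until database lock, so the change can go through the stated amendment route before any unblinding.

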#### Eligibility criteria

Adult patients (≥ 18 years) of both sexes and any race or ethnicity will be eligible for enrollment. Research personnel (physicians and research coordinators) will screen patients daily for eligibility daily under partial HIPAA waiver using the electronic medical record (EMR; Epic, Madison, WI, USA) to facilitate identification of SARS CoV-2-positive patients who may meet other eligibility criteria for the trial. Enrollment is feasible any time during the hospital stay; however, if hospital discharge is anticipated within 24 h the patient will not be enrolled. Patients previously screened and not meeting inclusion criteria or with exclusion criteria may be rescreened daily until eligibility expires (> 10 days post admission).

Initial screening will assess for evidence of HARF plus evidence of active SARS CoV-2 infection. Only patients positive for SARS CoV-2 using antigen or PCR test within the 10 days prior to randomization will be eligible. Patients must also have a C-reactive protein > 32 mg/dl. Assurance of adequate peripheral or central venous access is a requirement. Female subjects of childbearing potential must have a negative pregnancy test upon study entry.

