#### Outcomes

The primary goals of SCARLET are to establish the safety of citicoline in hospitalized SARS CoV-2-infected patients with HARF, to generate preliminary evidence of efficacy, and to identify an optimal citicoline dose for Phase 3 efficacy trials. There are therefore both safety- and efficacy-related primary outcome measures.

A particular dose of citicoline will be considered safe if the number of SAEs attributable to that citicoline dose (in the view of treating clinicians) remains below the threshold indicative of excessive toxicity once all 20 subjects have been treated (see Table 2).

**Table 2 Tab2:** Number of patients with SAEs required to claim excessive toxicity

No. of patients	1–2	3–4	5–7	8–10	11–14	15–17	18–20
No. with SAEs	–	2	3	4	5	6	7

The primary clinical outcome is a statistically significant difference in lowest recorded S_p_O_2_:F_i_O_2_ (S:F) ratio on study day 3, at *P* < 0.05. The lowest S_p_O_2_ for the day will be identified and used to generate the S:F ratio (based on the F_i_O_2_ at time of lowest S_p_O_2_ value).

Secondary/exploratory outcomes will be evaluated to identify statistically significant differences (*P* < 0.05) in (1) Lowest recorded S:F value on study days 1–2 and 4–8, or until extubation (whichever comes first); (2) Lowest Sequential Organ Failure Assessment (SOFA) score on study days 1, 3, 5, and 8; and (3) Highest COVID Ordinal Outcomes Scale score on study days 1, 3, 8, 15, and 29. On study day 29, we will also assess (1) Oxygen-free days through day 28; (2) Ventilator-free days through day 28; (3) ICU-free days through day 28; and (4) Hospital-free days through day 28.

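### The primary analysis gives discharge before day 3 the same survivor-stratum rule as death, so patients discharged alive have no proper place in the day 3 S:F comparison

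*Protocol article*

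**What the plan says.** The Outcomes section makes the lowest S:F ratio on study day 3 the primary clinical outcome: "The lowest S_p_O_2_ for the day will be identified and used to generate the S:F ratio". The Statistical analysis section tests it by analysis of variance, or by Kruskal–Wallis if the assumptions fail. If the global test rejects, "Follow-up contrasts comparing each dose to control will be performed at" α = 0.05/3.

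For patients who leave before day 3 it says: "If subject dropout due to mortality or discharge is present prior to day 3, the survivor average causal effect will employ" a potential-outcomes approach. The target is the average effect "among participants who would survive regardless of their intervention status, e.g., the always-survivors". The same section opens with "All analysis will be based on intention to treat guidelines" and states how the result will be used: "The recommended citicoline dose for Phase 3 trials will be the dose achieving the greatest statistically significant improvement in day 3 S:F ratios", with key secondary endpoints also considered.

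Three other places bear on the point:
- Eligibility criteria allow enrolment at any time in the hospital stay, except that "if hospital discharge is anticipated within 24 h the patient will not be enrolled".
- Participant timeline describes only a day 29 call about vital status and location for patients discharged home. It mentions no S:F measurement after discharge.
- The sample-size paragraph (under Protocol modifications) allows 5% missing data at day 3.

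**The concern.** Death before day 3 leaves the S:F ratio undefined, and a survivor stratum is a recognised answer to that. Discharge alive is a different event. The patient has survived, and the last readings before leaving are usually good.

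The rule can be read in two ways, and it fails on both:
- If discharge counts as not surviving, the stratum no longer consists of always-survivors, and the quickest recoverers are removed by definition.
- If discharge does not count, these patients can be always-survivors whose day 3 value is missing. A survivor average causal effect defines a population; it does not supply that value.

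Nothing else in the protocol fills the gap. The competing-risks analysis is for time-to-event outcomes, and the mixed and joint models are for repeated assessments. Neither is assigned to the day 3 comparison. At stake are the primary efficacy result and the dose taken to Phase 3: a dose that sends more patients home early would lose the most favourable outcomes.

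**Working it through.** **The plan's own figure.** The sample-size paragraph says "there is 80% power" at α = 0.05 for a standardized difference d = 0.9 between one arm and control (0.39 overall), with 80 participants and 5% missing. For one of four equal arms differing by d, f = d√3/4 = 0.9 × 1.732/4 = 0.390. With N = 80 × 0.95 = 76, the noncentrality is f²N = 0.39² × 76 = 11.56. On 3 and 72 degrees of freedom this gives power 0.802, so the figure reproduces. The same paragraph's 24 per group does not fit 80 in total; that is a separate matter, and 20 per arm is used here.

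**Illustration of the selection.** This is a complete-case calculation, not the planned estimator.
- From the protocol: d = 0.9, 20 per arm, α = 0.05/3 (taken as two-sided).
- Assumed: share p of placebo patients discharged before day 3; correlation ρ between a discharge marker and day 3 S:F; a common discharge threshold c = Φ⁻¹(1 − p).

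Share discharged on the dose = 1 − Φ(c − 0.9ρ).

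Difference among those still in hospital = 0.9 − ρ[φ(c − 0.9ρ)/Φ(c − 0.9ρ) − φ(c)/Φ(c)].

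Example, p = 10%, ρ = 1: c = 1.282 and c − 0.9 = 0.382. The bracket is 0.572 − 0.195 = 0.377, so the difference is 0.9 − 0.377 = 0.52 SD.

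| Placebo discharge p | ρ | Dose-arm discharge | Difference (SD) |
|---|---|---|---|
| 5% | 0.5 | 12% | 0.84 |
| 5% | 0.7 | 16% | 0.78 |
| 5% | 1.0 | 23% | 0.62 |
| 10% | 0.5 | 20% | 0.82 |
| 10% | 0.7 | 26% | 0.73 |
| 10% | 1.0 | 35% | 0.52 |

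**Power for one contrast** (α = 0.05/3, 20 per arm, p = 10%, simulated). With every value observed, the exact t-test power is 0.635.

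| ρ | Discharged removed | Discharged ranked best |
|---|---|---|
| 0.5 | 50% | 48% |
| 0.8 | 37% | 54% |
| 1.0 | 23% | 58% |

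The first two rows use a t test when discharged patients are removed and a rank-sum test when they are ranked. The last row uses a rank-sum test for both.

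**Anchored to the plan's 5%.** Let all of the 5% be discharge, averaged over placebo and one dose: ½[1 − Φ(c)] + ½[1 − Φ(c − 0.9ρ)] = 0.05.

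| ρ | Placebo / dose discharge | Difference (SD) | Power, removed | Power, ranked best |
|---|---|---|---|---|
| 0.5 | 2.8% / 7.2% | 0.86 | 59% | 57% |
| 0.8 | 1.8% / 8.2% | 0.80 | 54% | 58% |
| 1.0 | 1.2% / 8.8% | 0.76 | 51% | 59% |

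Simulated powers carry an error of one to two points.

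**A perfectly estimated stratum.** Take the patients who would still be in hospital on either arm, with ρ = 1.
- Constant effect: the stratum effect is 0.90, with no bias, but the stratum holds only 77% of patients at p = 5% and 65% at p = 10%.
- Unequal effect, 45% gaining 2 SD and the rest nothing (mean 0.45 × 2 = 0.90): the stratum effect is 0.48 at p = 5% and 0.35 at p = 10%.

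**The case against.** The strongest reply is that the complete-case figures describe an analysis the protocol does not propose. A survivor average causal effect is meant to replace the naive comparison of those still present, and with a constant effect a correctly estimated stratum effect is unbiased for its stratum. This stands. A reader might infer that the plan makes a working dose look weaker. The protocol does not support that as a certainty: dilution needs better oxygenation to drive discharge and either a naive comparison or a treatment effect that varies between patients. A larger effect in the sickest patients could offset it.

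A reader might also infer a flat contradiction of intention to treat. That is too strong. A principal stratum is defined on potential outcomes under each arm, not on observed status; analysis of variance or Kruskal–Wallis is the base analysis; and the text does not say whether the survivor effect replaces or supplements it. What remains is a poor fit.

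The exposure may be small. The only planning figure is 5% missing, and these are patients with hypoxemic respiratory failure on a planned 5-day course. It would be wrong to count every discharge between 24 and 72 h as lost: a patient who leaves during day 3 has a day 3 value, and when day 3 begins depends on day numbering. Early discharge also counts in hospital-free days, in the competing-risks analysis and, through secondary endpoints, in dose choice.

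None of this gives a patient discharged alive before day 3 a place in the primary comparison. The problem is a stated rule that does not fit the event, not detail left to an analysis plan.

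**Conclusion.** The point holds as a mis-specified rule: an always-survivor estimand cannot handle discharge alive, on either reading, and no other section repairs it.

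The likely consequence is fewer patients and less power, with possible dilution of the effect. Under the assumed 5–10% placebo discharge and ρ from 0.5 to 1.0, the complete-case difference falls from 0.90 to about 0.84–0.52 SD. With total early discharge near the plan's 5%, it is 0.86–0.76 SD, and ranking discharged patients best changes power by between −2 and +8 points. The protocol gives neither the discharge rate nor its link with S:F, so these figures show a range and do not predict this trial's result.

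The case for change rests first on the estimand and the dose decision that depends on it, and only second on power. It is a specific, inexpensive correction to the analysis text. It does not show that the design is unsound.

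**What to change.** Before unblinding, replace the single rule with separate ones:

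- Keep all randomized patients in the primary day 3 comparison.
- For a patient discharged alive before day 3, carry forward the last recorded S:F before discharge, or assign a prespecified favourable rank. Name one of these as primary. If it is the S:F value, state which reading is meant; the lowest value on the last in-hospital day would match the endpoint definition.
- Give deaths before day 3 the worst rank.
- Compare arms with the rank test already in the plan, and report a mean S:F difference beside it.
- Retain the survivor average causal effect for death only, as a sensitivity analysis.

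The cost is analysis wording, with no new data collection. The downsides are real. The estimand becomes composite or rank-scale, and a best rank would place a patient sent home on oxygen above one breathing room air in hospital. The rank version gains power only when discharge tracks S:F closely: at ρ = 0.5 and 10% placebo discharge it gives 48% against 50%. Fixing the rule in advance also prevents a data-driven choice on the primary outcome.

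### The SOFA comparison is worded as an unadjusted non-parametric test although Time 0 SOFA is calculated: valid, but it gives up precision in an endpoint named for the Phase 3 dose choice

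*Protocol article*

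**What the plan says.** - Participant timeline: "baseline Sequential Organ Failure Assessment (SOFA) and COVID Ordinal Outcomes Scale (HRS) scores will be calculated at Time 0". Time 0 is the time of consent, and the first dose follows it, so the score is a true baseline.
- Outcomes: the secondary/exploratory outcomes include "Lowest Sequential Organ Failure Assessment (SOFA) score on study days 1, 3, 5, and 8".
- Statistical analysis, on SOFA: "Differences in SOFA scores between groups will be evaluated using non-parametric tests". The sentence names neither a baseline term nor a change score.
- Statistical analysis, on dose choice: the Phase 3 dose is the one with the largest significant gain in day 3 S:F, "with consideration of key secondary endpoints (SOFA scores, etc".
- Statistical analysis, on repeated outcomes: "For outcomes with repeated assessments, generalized mixed models will evaluate differences between groups with a subject-level random effect", followed by "The mixed model accounts for data that are missing at random, when including baseline covariates associated with missing status".
- Randomization and blinding: 1:1:1:1 allocation in permuted blocks of varying size, with no stratification factor named. Balance at baseline is to be described by standardized mean differences, and no adjustment is tied to the result.

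**The concern.** SOFA at follow-up depends in part on SOFA at entry. The Discussion itself stresses how widely COVID-19 varies in severity. With 20 per arm and no named strata, the design does not balance entry SOFA beyond what chance gives, so only the analysis can account for it. The SOFA sentence names a class of test that, as usually run, takes no covariate, so a baseline value that is to hand goes unused.

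Two things are at stake. A real SOFA effect is harder to detect. And a dose arm that happens to start less ill looks somewhat better on the one secondary endpoint named for the dose choice. That matters most when the doses look alike on S:F.

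**Working it through.** **The plan's own figure.** The only power statement concerns day 3 S:F: 80% at effect size 0.9 for one arm against control, or 0.39 overall. One arm displaced by 0.9 SD among four gives f = 0.9 × √3 / 4 = 0.390. A four-group F test at 0.05 with 80 × 0.95 = 76 evaluable patients has 80.2% power, so the figure reproduces. No power is stated for SOFA.

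**Inputs from the protocol.** 20 per arm (Study design and setting), and 5% missing at day 3 (sample size text, under Protocol modifications), so 20 × 0.95 = 19 evaluable per arm. The sample size text also mentions 24 per group, which does not fit 80 in four equal arms; 20 is used here.

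**Assumed, not in the documents.** A SOFA effect of 0.7 SD, and a correlation r between Time 0 and follow-up SOFA of 0.3 to 0.7. The score is simulated as an integer from 0 to 24 with mean 6 and SD 2.5. Tests are pairwise, two-sided, at 0.05.

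**Power.** Adjusting for baseline multiplies the residual variance by 1 − r². For a normal outcome the effective effect is therefore 0.7 / √(1 − r²). The t-based columns use this formula. The rank columns come from simulation (Mann-Whitney against rank analysis of covariance), and repeated runs move by about one point.

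| r | 1 − r² | t test, unadjusted | t-based, adjusted | Rank test | Rank analysis of covariance |
|---|---|---|---|---|---|
| 0.3 | 0.91 | 56% | 60% | 52% | 56% |
| 0.5 | 0.75 | 56% | 68% | 52% | 63% |
| 0.6 | 0.64 | 56% | 75% | 52% | 68% |
| 0.7 | 0.51 | 56% | 84% | 52% | 78% |

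The gain for the rank analysis is about 4, 11, 16 and 26 points. With no treatment effect, both rank methods rejected in about 5% of simulated trials (4.5% to 5.3% over 10,000 trials per setting).

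**Chance imbalance at Time 0, 20 per arm.** The standard error of a difference between two arm means is √(2/20) = 0.316 SD. With c the threshold in SD, the chance that at least one of three doses starts healthier than placebo by more than c is 1 − ∫ φ(z) Φ(z + c√20)³ dz, because all three share one placebo mean.

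- c = 0.4: about 22% in the healthier direction, 44% counting either direction.
- c = 0.5: about 13% in the healthier direction, 27% counting either direction.

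**How much reaches the outcome.** An imbalance of c shifts the unadjusted contrast by r × c. For c = 0.4 that is 0.4 × 0.3 = 0.12 SD up to 0.4 × 0.7 = 0.28 SD.

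**The case against.** - **An unadjusted randomized comparison is not wrong.** This stands. Type I error is held, and chance imbalance is already part of the test's sampling error. A reader might infer that the SOFA result would be biased or invalid; neither the documents nor the simulation supports that.
- **The wording is generic, and rank analysis of covariance can itself be called non-parametric.** This stands in part. The sentence does not forbid a covariate, but its ordinary reading is a Mann-Whitney or Kruskal-Wallis test on follow-up scores, and nothing in it points to the baseline.
- **Mixed models are planned for repeated outcomes, and SOFA is one.** This stands in part. The non-parametric test is not the only planned look at SOFA. But baseline covariates are mentioned there only where they relate to missingness, Time 0 SOFA is not named, and the text does not say which SOFA analysis leads.
- **The COVID Ordinal Outcomes Scale.** A reader might extend the point to the sentence "A multinomial ordinal proportional odds model will estimate the odds ratio between study groups for COVID Ordinal Outcomes Scale". The text does not support that as an error. It lists no covariates and excludes none, and an article commonly leaves a model's covariate list to the SAP, which is not shown.
- **Dose choice.** A reader might infer that SOFA could decide the dose. It cannot on its own: day 3 S:F leads and SOFA is only considered. The ordinal scale is not named there.
- **The gain depends on r.** This stands. At r = 0.3 it is about 4 points.

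**Conclusion.** The point holds as a loss of precision in one secondary analysis, not as an error of validity. The SOFA test as worded leaves out a baseline score that the trial calculates anyway. For an assumed 0.7 SD effect with 19 per arm, the cost is about 4 power points at r = 0.3 and about 26 at r = 0.7. Neither the effect size nor the correlation is in the documents, so the range matters more than any single figure. The chance of a favourable start above 0.4 SD in at least one dose arm is about 22%, and at r up to 0.7 no more than 70% of such a gap reaches the SOFA contrast. The consequence for dose choice is real but limited, since SOFA only supports a decision led by day 3 S:F.

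**What to change.** Reword the SOFA sentence so that the comparison is a rank analysis of covariance with Time 0 SOFA as covariate; a proportional odds or mixed model with the same covariate would also serve. Use the Time 0 score and not the day 1 score, which is listed as an outcome. State that this adjusted analysis, rather than an unadjusted test, informs the dose choice, and say how it relates to the planned mixed model.

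Optionally, for consistency and not because the text is in error, use the Time 0 ordinal score as covariate in the proportional odds model.

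The cost is a wording change made before unblinding. No new data, visits or patients are needed.
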